### Secondary outcomes

The scores on the repeated continuous secondary outcomes (e.g. PEM, EQ-5D-5L, AROM, Grip strength, Splint adherence) will be compared between the randomised groups using a similar longitudinal mixed effects linear regression model as described for the analysis of the primary outcome. Treatment effects for each protocol stipulated follow-up points will also be presented.

Adherence to the randomised splint treatment during the first 6 weeks post-randomisation will be estimated from the heat sensor in the splint. Adherence will be summarised for each randomised group using a variety of summary measures (e.g. mean number of hours per day wearing the splint) and mean adherence compared between the group using a linear regression model. As with the primary outcome, three treatment effect contrasts and their associated confidence intervals will be estimated and reported from the model: (1) long vs short splint, (2) long vs mini splint, (3) mini vs short splint.

### Economic evaluation

The health economic analysis will estimate the costs and QALYs of each of the splints and will be conducted in two parts. First, a within-trial cost-effectiveness analysis (i.e. economic evaluation alongside clinical trial (EEACT)) will be performed, and second, an analysis of the long-term cost-effectiveness will be conducted using a de novo decision analytic model. The cost-effectiveness of three splints will be estimated as incremental cost-effectiveness ratios (ICERs) using full incremental analysis, accounting for any dominance. In the within trial analysis, QALYs will be estimated by calculating the area under the curve for health utility using the EQ-5D-5L, and the costs will be estimated for the health service resource use up to 1 year multiplied by national average costs. Long-term cost-effectiveness modelling will use the data from the RCT (on proportions of patients with complications and adverse events) to estimate the lifetime QALYs and costs. Sensitivity analyses will explore the potential impact of parameters upon costs, QALYs and ICERs. Parameter uncertainty will be included in probabilistic sensitivity analysis based on Monte Carlo simulation. Cost-effectiveness acceptability curves (CEACs) will be plotted to identify the probability of each splint being cost effective for a range of threshold values for an additional QALY.

### Process evaluation

The MRC framework states that process evaluations should inform practice through answering three questions about how interventions work [21]:What is implemented?How does context affect implementation and outcomes?How did the effects of each intervention occur (mechanisms of impact)?

The process evaluation sub-study aims to answer the above questions via the following objectives:Collecting data on adherence to splint prescriptionCollecting patient-reported data on (‘stated’) preferences for particular splint attributes, at baselineCollecting patient-reported data on (‘revealed’) preferences and splint acceptability at 6 weeksConducting qualitative interviewsDeveloping a structural equation model, to show the effect of baselines, preferences, acceptability, and adherence on pain/function (PRWHE: RCT primary outcome)

### Interim analyses {21b}

There is no planned interim analysis, beyond checking the recruitment and retention rate at the end of the pilot phase.

### Methods for additional analyses (e.g. subgroup analyses) {20b}

Subgroup analyses will be performed to explore whether there is heterogeneity in treatment effect for the primary endpoint across the following pre-specified subgroups: sex, employment type, eligibility for occupational sick pay, age category, zone of injury, and tendons repaired.

The subgroup analyses will be performed on the ITT population only. The analysis will be based on the primary analysis model with the addition of an interaction term between the treatment and subgroup to assess the stability of the result in different populations. For simplicity, the interaction between treatment and time will be excluded from this model. Treatment effect estimates for the mean PRWHE post-randomisation scores with 98.3% confidence intervals will be calculated for each sub-group. The results will be displayed graphically using forest plots. No *p*-values will be presented, as it is acknowledged that the trial is not powered for these subgroup analyses, and they are considered exploratory.

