#### Sample size {14}

The sample size was calculated using the methodology and formula for repeated outcome measures [16]. We assumed the following: (i) 90% power; (ii) 1.67% two-sided significance level (to allow for three head-to-head comparisons between the three randomised groups); (iii) 1 baseline and 4 repeated assessments at 6, 12, 26, and 52 weeks post-randomisation; (iv) a target difference of 6 points [17, 18] in the post-randomisation mean PRWHE scores between any two of three groups; (v) a standard deviation of 20 points for the PRWHE outcome at each post-randomisation time point [9, 16–18]; (vi) an exchangeable correlation or compound symmetry of 0.50 between the repeated PRWHE assessments at 6, 12, 26, and 52 weeks post-randomisation [9, 18]; (vii) 20% attrition. With these input parameters, 114 participants per group are required (3 × 114 = 342 in total). After allowing for 20% attrition, we propose to randomise 429 participants in a 1:1:1 ratio (143 long splint: 143 short splint: 143 mini splint).

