### Methods in analysis to handle protocol non-adherence and any statistical methods to handle missing data {20c}

The impact of missing PRWHE outcome data will be minimised to some extent by using the linear mixed model, which allows the inclusion of intermittent responders in the primary analysis. PRWHE scores for complete and intermittent responders will be compared descriptively. The impact of missing data will additionally be assessed using multiple imputation by chained equations (MICE). Missing outcome and covariate data will be predicted by age, rupture rate, hand dominance, available PRWHE data at other follow-up time points, and any baseline covariates found to be predictive of the outcome data. The estimates of the treatment effects and their associated confidence interval from the imputation model will be graphically displayed alongside the results for the observed data. Additional sensitivity analysis will consider scenarios whereby participants with missing data have outcomes worse than those with available data (missing not at random scenarios). The primary analysis approach will be based on the as-randomised population, analysing participants in their randomised groups regardless of adherence to their randomised intervention.

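### Splint-by-age heterogeneity is planned only by age category; a continuous age interaction would use the same data more efficiently, by an amount that depends on bands not yet stated

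*Protocol article*

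**What the plan says.** The protocol article's section on additional analyses {20b} lists the subgroup factors as "sex, employment type, eligibility for occupational sick pay, age category, zone of injury, and tendons repaired". The method is "the primary analysis model with the addition of an interaction term between the treatment and subgroup". On reporting it says: "Treatment effect estimates for the mean PRWHE post-randomisation scores with 98.3% confidence intervals will be calculated for each sub-group", shown as forest plots. It also limits what is claimed: "No *p*-values will be presented, as it is acknowledged that the trial is not powered for these subgroup analyses", and it calls these analyses exploratory.

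The number of age bands and their cut-points are not given, and no interaction with age as a continuous variable is mentioned. The section on statistical methods leaves full details to a separate SAP, to be finalised before follow-up ends.

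The section on missing data {20c} names age without the word category: "Missing outcome and covariate data will be predicted by age, rupture rate, hand dominance". Eligibility requires a minimum age of 16. The article does not say outright that age is stored in years, but these two places make it very likely.

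**The concern.** Age is the one factor on the list that is naturally a continuous measurement. A treatment-by-category interaction assumes one splint effect for everyone within a band and a jump at each boundary. A gradual change in effect with age may then be missed, or appear as a step whose position and size depend on the cut-points.

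The trial concedes that it is not powered for subgroup questions, so precision here is scarce. What is at stake is how much can be learned about whether older and younger patients respond differently to the three splints. The primary comparison is not at stake.

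**Working it through.** **1. Reproduce the plan's own figure.** The sample size section {14} gives "a target difference of 6 points", "a standard deviation of 20 points for the PRWHE outcome at each post-randomisation time point", correlation 0.50, one baseline and four follow-up assessments, 90% power, and a "1.67% two-sided significance level (to allow for three head-to-head comparisons between the three randomised groups").
- Variance factor for the mean of four follow-ups adjusted for baseline: (1 + 3 × 0.5)/4 − 0.5² = 0.625 − 0.25 = 0.375.
- Effective SD: 20 × √0.375 = 12.25.
- Two-group comparison of means: 113 per group by the normal approximation, 114 by the noncentral t (power 0.9001). The plan states 114.
- Attrition: 114/0.8 = 142.5, rounded to 143; 3 × 143 = 429, as stated.

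The inputs can therefore be carried over to the interaction.

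**2. Information lost by banding.** For an effect that is linear in age, the share lost is 1 − (between-band variance of age / total variance of age). The age distribution is assumed. Results for equal-sized bands:

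| Assumed age shape | 2 bands | 3 bands | 4 bands | 5 bands |
|---|---|---|---|---|
| Uniform 16–80 | 25% | 11% | 6% | 4% |
| Truncated normal from 16 | 34% | 18% | 12% | 8% |
| Normal | 36% | 21% | 14% | 10% |
| 16 + gamma, shape 2 | 45% | 28% | 21% | 16% |
| 16 + gamma, shape 1.5 | 47% | 31% | 23% | 18% |

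The more extreme exponential shape gives 52%, 35%, 27% and 21%. Unequal bands can do worse: under the truncated normal, a single cut at 65 loses 74%.

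**3. Standard error of a pairwise splint-by-age slope, per SD of age, with 114 per group.**
- Continuous: 20 × √(2 × 0.375/114) = 1.62 points.
- Median split, normal age: the difference between halves has SE 20 × √(4 × 0.375/57) = 3.24. The halves' mean ages lie 1.596 SD apart, so the slope SE is 3.24/1.596 = 2.03.
- Three equal groups, normal age: 1.62/√0.793 = 1.82.

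In equivalent patients per group: 114 continuous, 114 × 0.793 = 90 with three bands, 114 × 0.637 = 73 with two.

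**4. Chance that the 98.3% interval for the slope excludes zero** (critical value about 2.39). The slopes are assumptions; the article gives none.

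| True slope, points per SD of age | Continuous | Median split, normal age |
|---|---|---|
| 2 | 12% | 8% |
| 3 | 29% | 18% |
| 5 | 75% | 53% |

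A slope of 5 is large: it means a 10-point change in the splint difference between one SD below and one SD above the mean age, against a 6-point target for the main comparison.

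**5. Do more bands solve it?** The small losses for four or five bands hold only if a linear trend is read across them. The plan reports one estimate per band. With equal bands, the 98.3% half-width is 2.39 × 20 × √(2 × 0.375/n per band): 5.5 points for two bands (n = 57), 6.7 for three (n = 38) and 8.7 for five (n = 22.8). From three bands on, the half-width exceeds the 6-point target difference.

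**The case against.** The case for leaving the plan alone has real content.

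- **The size of the loss is not in the document.** A reader might infer that the plan throws away a fifth to almost half of the information. The article does not support that as fact: it states no bands, cut-points or age distribution. Four or five equal bands of normal age lose only about 14% or 10%, and three bands of uniform age about 11%. This objection stands.
- **Bands have uses.** They need no linearity assumption, they match the display of the other five factors, and they serve the stated aim of checking how stable the result is across populations. This stands, and is why the forest plot should keep them.
- **No significance decision is planned.** The section presents no p-values, so the chance of excluding zero is only a measure of precision. Quoting 75% against 53% alone would flatter the change. At smaller slopes, age modification would usually be missed either way.
- **The SAP may cover this.** It is not shown and could set cut-points or add a continuous analysis. That limits the point. But the article does name a category as the moderator, and cut-points alone would not restore the information lost within bands.
- **The two mentions of age do not conflict.** A reader might see a contradiction between age as an imputation predictor and age category as a subgroup. There is none, since the two serve different purposes. The imputation text helps only to suggest that age is held in years.

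**Conclusion.** The point stands in a conditional form. As written, the plan explores age only in categories. If the splint effect changes roughly linearly with age and age is roughly normal, equal-sized banding costs about 36% of the information with two groups and 21% with three, and less with more. A median split of skewed age could cost up to about 47% under the gamma shapes tried. In the trial's own units, the slope SE rises from 1.62 to 1.82 (three groups) or 2.03 (two groups) points per SD of age.

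These figures rest on an assumed age distribution, equal-sized bands, linearity, 114 evaluable patients per group, and age being available in years. If the true change were a step at a chosen cut-point, the advantage of continuous age would shrink or reverse.

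The importance is low. This is one of six exploratory subgroup factors, and the primary model, its three contrasts and the sample size are unaffected.

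**What to change.** In the SAP, specify the exploratory age analysis with age as a continuous variable:
- Add linear treatment-by-age terms to the primary model, with a restricted cubic spline as a check of shape.
- Report the three pairwise splint-by-age slopes with 98.3% confidence intervals, without p-values, in line with the other subgroup analyses.
- Plot each splint difference, with its interval, against age.
- Keep age bands for the forest plot only, with cut-points fixed before the data are analysed.

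The cost is a few lines of SAP wording and one more plot, with no new data if age is held in years as expected. The downside is a linearity assumption, which the spline checks, though with limited precision at this sample size.

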### Methods in analysis to handle protocol non-adherence and any statistical methods to handle missing data {20c}

The impact of missing PRWHE outcome data will be minimised to some extent by using the linear mixed model, which allows the inclusion of intermittent responders in the primary analysis. PRWHE scores for complete and intermittent responders will be compared descriptively. The impact of missing data will additionally be assessed using multiple imputation by chained equations (MICE). Missing outcome and covariate data will be predicted by age, rupture rate, hand dominance, available PRWHE data at other follow-up time points, and any baseline covariates found to be predictive of the outcome data. The estimates of the treatment effects and their associated confidence interval from the imputation model will be graphically displayed alongside the results for the observed data. Additional sensitivity analysis will consider scenarios whereby participants with missing data have outcomes worse than those with available data (missing not at random scenarios). The primary analysis approach will be based on the as-randomised population, analysing participants in their randomised groups regardless of adherence to their randomised intervention.

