## Statistical methods

### Statistical methods for primary and secondary outcomes {20a} and additional analyses {20b}

Data will be reported and presented according to the CONSORT [19]. All analyses described below will be on the as-randomised (intention to treat) basis, unless specified otherwise. Full details of the statistical analysis will be provided in a separate statistical analysis plan (SAP) which will be finalised prior to the end of follow-up. The SAP will be made available on the trial ISRCTN site. The analysis will be conducted in accordance with CTRU SOPs.

The final analysis will take place after all follow-up has been completed.

Baseline demographic, physical and clinical characteristics, and health-related quality of life data will be described and summarised overall and for the three randomised groups.

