### Primary outcome

The primary outcome will be the mean post-randomisation total score on the PRWHE measured at 6, 12, 26, and 52 weeks post-randomisation. The primary effectiveness analysis will compare the post-randomisation PRWHE scores, between the three randomised groups, using a linear mixed model incorporating all post randomisation PRWHE scores (at 6, 12, 26, and 52 weeks) as outcomes, with random effects for centre and subject (to account for the repeated observations per patient), and fixed effects for randomised group, time post-randomisation, and baseline score [20]. We shall assume an exchangeable correlation between the repeated measurements.

Three treatment effect contrasts will be estimated and reported from the linear mixed model: (1) long vs short splint (2); long vs mini splint (3); mini vs short splint. We will estimate 98.3% confidence intervals for the three treatment effects for simultaneous inference and to ensure that all parameters are covered with 95% confidence. This model will include all patients who provide valid PRWHE data for at least one post-randomisation follow-up time point.

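### The stated imputation model omits randomised group, so the missing-data sensitivity analysis, run as written, pulls real treatment differences towards zero

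*Protocol article*

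**What the plan says.** The primary analysis (Statistical methods, Primary outcome) is a linear mixed model "with random effects for centre and subject (to account for the repeated observations per patient), and fixed effects for randomised group, time post-randomisation, and baseline" PRWHE score. Its analysis set is defined thus: "This model will include all patients who provide valid PRWHE data for at least one post-randomisation follow-up time point".

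The section on non-adherence and missing data {20c} adds chained-equations imputation as a further assessment of missing data. It names the predictors: "Missing outcome and covariate data will be predicted by age, rupture rate, hand dominance, available PRWHE data at other follow-up time points", and then "any baseline covariates found to be predictive of the outcome data". The treatment effects "from the imputation model will be graphically displayed alongside the results for the observed data". The same section also plans missing-not-at-random scenarios in which "participants with missing data have outcomes worse than those with available data".

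Randomised group is not in the predictor list, and nothing in the article says that imputation is done within arm. The statistical methods section leaves full detail to a separate SAP, which is not at hand.

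**The concern.** An imputation model should contain at least the terms of the analysis model it serves, above all the term being estimated. If arm is left out, a missing score is drawn from a distribution shared by all three arms, given the scores that were observed. Imputed participants then carry only as much treatment difference as leaks through their other PRWHE scores, and none if they have no follow-up score.

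The open-ended clause does not repair this. Allocation is not a baseline covariate, and its inclusion should not depend on whether it turns out to be predictive.

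What is at stake is the reading of the planned plot. A gap between the imputed and observed-data estimates would partly reflect how the imputation was built, yet it could be taken as sensitivity to the missing data.

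**Working it through.** **Inputs** (Sample size {14}): difference 6, SD 20, exchangeable correlation 0.50, 20% attrition, one baseline and four follow-up scores, 90% power, 1.67% two-sided.

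**Assumptions:** the 0.50 also applies to baseline; the arm difference is constant over visits; data are missing at random within each pattern; the predictors are baseline PRWHE and PRWHE at the other visits. Age and hand dominance are unrelated to arm by randomisation. Rupture occurs after randomisation and could carry a little information on arm; it was not modelled.

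**Step 1: the plan's own figure.** The variance factor is R = (1 + 3 × 0.5)/4 − 0.5² = 0.375. Then n = 2 × (2.393 + 1.282)² × 400 × 0.375 / 36 = 112.5, so 113 per group against 114 stated (power at 114 is 90.4%). 114/0.8 = 142.5, rounded up to 143, and × 3 = 429. The inputs are therefore read correctly, including the baseline correlation: without baseline adjustment the factor is 0.625 and n is 188.

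**Step 2: attenuation by hand, equal missingness.** Regressing a missing score on k observed scores gives each a coefficient of 0.5/(1 + (k − 1) × 0.5). With arm left out, the arm difference in an imputed score is that coefficient × the number of observed follow-up scores × 6. (The small between-arm part of the pooled covariance is ignored.)

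| Missing 20% have | k | Coefficient | Difference per imputed score | Their 4-visit mean | Overall |
|---|---|---|---|---|---|
| no follow-up score | 1 | 0.50 | 0 | 0 | 0.8 × 6 + 0.2 × 0 = 4.8 |
| week 6 only | 2 | 0.33 | 2 | (6 + 3 × 2)/4 = 3 | 0.8 × 6 + 0.2 × 3 = 5.4 |
| weeks 6 and 12 only | 3 | 0.25 | 3 | (6 + 6 + 3 + 3)/4 = 4.5 | 0.8 × 6 + 0.2 × 4.5 = 5.7 |

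At week 52 alone, loss after week 6 gives 0.8 × 6 + 0.2 × 2 = 5.2.

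**Step 3: simulation.** Chained-equations imputation, five imputations, 10,000 per arm, 10 replicates, ANCOVA on the 4-visit mean. True effects are long 0, short 0, mini −6. Cells show mini − long, then mini − short; simulation SEs are 0.03 to 0.09.

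| Pattern, 20% in each arm | Group omitted | Group included |
|---|---|---|
| no follow-up score | −4.91, −4.76 | −6.03, −6.02 |
| intermittent, 20% per visit | −5.50, −5.47 | −5.98, −6.00 |
| dropout building to 20% by week 52 | −5.42, −5.50 | −5.93, −5.90 |
| lost after week 6 | −5.34, −5.37 | −5.97, −6.02 |

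The simulation agrees with the hand results, and including group restores about 6.

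**Step 4: unequal missingness.** Assume 30% (long), 10% (short) and 20% (mini) have no follow-up score, with long = short in truth. The pooled observed mean relative to long is −6 × 0.8/(0.7 + 0.9 + 0.8) = −2.0. The short − long contrast becomes 0.1 × (−2) − 0.3 × (−2) = +0.4. Simulation gave +0.46 (SE 0.05), against −0.13 with group included. With gradual dropout it gave +0.16 (SE 0.04), against −0.11 with group included.

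**Step 5: centre.** With group kept in and centre left out, a true −6 came back as −6.0, −5.9 and −6.0 at assumed intraclass correlations of 0.02, 0.05 and 0.10 (SE 0.03). Allocation is stratified by site, so arms are balanced within centre and no shrinkage is expected.

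**The case against.** The strongest reply is that the exact imputation equations are ordinary SAP content. The article never says that arm is excluded, and baseline PRWHE is not named either, so the list could be read as auxiliary variables added to those of the analysis model. This stands as a reason for caution: if the SAP includes group or imputes by arm, the problem is already solved. It does not clear the article, which does not leave the predictors open but states what they will be. Baseline PRWHE can enter through the clause on predictive baseline covariates; randomised group cannot.

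The second reply concerns size, and much of it stands. The drop to 4.8 needs participants with no follow-up score at all. The retention section {18b} counts a participant as lost only if the week 52 questionnaires are not returned, and it provides for remote completion and repeated contact. The primary analysis leaves out people without any follow-up score, and nothing says that the imputation will bring them in. Under partial missingness the shift is about 0.3 to 0.6 points. With 114 per group the standard error is √(2 × 400 × 0.375/114) = 1.62 and the 98.3% half-width about 2.39 × 1.62 = 3.9, so the shift is roughly 8 to 15% of that half-width. It would seldom change a conclusion by itself. It is, however, a systematic displacement between two estimates from the same trial, in the plot meant to show whether missing data matter.

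A reader might also infer that the missing-not-at-random check is empty, because a penalty common to all arms cancels when missingness is balanced. The article does not say that the penalty is common; it speaks of scenarios in the plural, and a penalty applied in one arm at a time would move the contrasts. Nor does the term used for rupture show an error: ruptures are recorded for each participant as serious adverse events, so it is loose wording.

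**Conclusion.** Wrong as written; should-fix. The stated predictor list omits the term that the analysis estimates. If it is the whole model and missingness is similar across arms, a true 6-point contrast falls to about 5.4 to 5.7 (5 to 10% lower) under the partial-missingness patterns worked by hand. It falls to about 4.8 (20% lower) if the missing 20% have no follow-up score and are imputed. The documents give only the 20%; the patterns and the arm-specific rates are assumptions.

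Three stronger readings are not supported:

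- **Omitting centre also shrinks the contrasts.** It does not, by the check above; centre matters for compatibility with the analysis model.
- **Every contrast moves towards zero.** That holds for non-zero contrasts with similar missingness. With unequal missingness a null contrast can move away from zero, so the error is not reliably conservative.
- **The trial's main result is at risk.** The primary mixed model contains randomised group and does not use the imputations, so the primary estimate, power and error rate are untouched.

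**What to change.** State in the SAP, and in the protocol at its next revision, that imputation is run separately by randomised arm or includes randomised group as a predictor in every imputation equation. Add the other analysis-model variables by name: baseline PRWHE, and centre for compatibility. With 143 per arm over 26 sites (143/26 = 5.5 per arm per site), centre indicators within arm would be sparse, so entering group as a predictor may be the simpler route. State also whether participants without any follow-up score are imputed, since the size of the effect depends on it.

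The cost is a sentence or two and a minor change of code. No data collection changes. The article has the SAP finalised before follow-up ends, so the text belongs there; if the SAP already specifies group or imputation by arm, only the article's list needs aligning.
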